#### Neonatal Outcomes

The birthweight, and the presence of hypoglycemia will be compiled from the newborn medical records.

#### Fertility Outcomes

The clinical pregnancy rate, spontaneous abortion rate, and the live birth rate will be compiled from the patient medical records.

### Participant Timeline

The participant timeline has been summarized in Figure 1.

**Figure 1 F1:**
[figure not shown]
Participant timeline.

### Sample Size Calculation and Analysis Plan

#### Sample Size Calculation

Since no minimally clinically important effect size has been defined for the HEI score, our effect size has been estimated as a plausible effect of the intervention based on the preliminary results of the *Obesity Fertility* trial (71), which demonstrated a 12.5 ± 13.0 points increase in the average HEI score of women with obesity and infertility after a 6-month lifestyle intervention (unpublished data). An increase of 12 points in the average HEI score was also observed in breast cancer survivors with obesity who received a 6-month dietetic intervention (75). To detect a 10% difference in the average HEI score between groups with a 13-point standard deviation, an alpha value of 5% and 80% power, we will need to recruit 27 women per group (76). To account for a 20% attrition rate (77), a total of 68 women and their partners will be recruited.

#### Statistical Analysis Plan

Study results will be analyzed at the end of the trial following intent-to-treat principles. Participants' baseline characteristics will be reported to assess group comparability at baseline in preconception and at the beginning of pregnancy. A statistical significance threshold of 5% will be used for all analyses. Statistical analyses will be performed using the Statistical Package for the Social Sciences (SPSS version 26) and R (Version 4.0.2) software. No interim analysis will be performed.

#### Primary Outcome Analysis

Our primary endpoint is the difference in the evolution of the HEI score between study groups in time, which will be assessed using a mixed linear model of the HEI score integrating the effects of time as a continuous variable, study group, and the interaction between the study group and time. This statistical model has been chosen because it will allow us to account for (1) the different lengths of preconception follow-up that will arise as a result of women becoming pregnant throughout the study; and (2) variable timing and number of the *R24W* questionnaires performed by the participants (due to non-adherence to the protocol) (78). The average HEI score in each group at 2, 4, and 6 months will also be compared using standard mixed-model repeated measures ANOVA with *post-hoc* Student's *t*-tests with Bonferroni correction for multiple comparisons. As a secondary analysis, Kaplan-Meier survival curves of women who have increased their HEI score by 10 points or more will be produced, with censoring for dropout or occurrence of pregnancy.

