### Trial Design and Setting

This study is a multicenter open label parallel group randomized controlled trial coordinated at the Research Centre of the Centre hospitalier universitaire de Sherbrooke (CR-CHUS) in Sherbrooke, Quebec, Canada. The Province of Quebec has a population of 8.5 million. In 2014 overweight and obesity rates were 27 and 15% for adult women and 41 and 18% for adult men, respectively (49). Participants will be recruited from the Sherbrooke and Quebec City regions. The obstetrical care of women from Sherbrooke and Quebec City is provided by general practitioners, midwives, and obstetricians in outpatient clinics. The CHUS is a regional tertiary care center where ~2,800 deliveries are performed annually. The CHU de Québec Université Laval is a regional tertiary center where ~7,500 deliveries are performed annually at two sites, the Centre Hospitalier de l'Université Laval and the Hôpital Saint-François d'Assise.

An explanatory design has been chosen to rigorously evaluate the potential benefits of the *Healthy for my Baby* intervention (50). Masking of the research team and participants to the intervention will not be possible given the nature of the study. Couples will be randomized to the intervention or control group in a 1:1 ratio. The randomization list was generated independently by the CRCHUS' biostatistics service using a computerized unstratified blocked randomization with blocks of random sizes 2–6. The group allocation sequence was sent directly to the mobile application programming team who input it into the mobile application software. The mobile application website is hosted on the PIERCE server, a secured research platform developed by the local CRED medical informatics working group. Once participants have provided written consent, completed the trial enrollment form, and completed baseline assessment, their mobile application profile will be created by the research assistant which will trigger randomization to a treatment group. Participants will receive the result of their group allocation by email with a link to install the appropriate version of the mobile application.

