#### Lifestyle Habits

##### Diet Quality

Diet quality will be measured using the *Canadian Healthy Eating Index* 2007 (C-HEI 2007) which is a 100-point score adapted from the American HEI-2005 to measure adherence to the 2007 Canadian Food Guide (57, 58). The C-HEI 2007 score will be measured at baseline, 2, 4, and 6 months in preconception and each trimester in pregnancy with the *R24W*, an online 24-h dietary recall tool available in French and English, and validated for both pregnant and non-pregnant individuals of the French-Canadian population (59, 60). Three dietary recalls will be used to compile the C-HEI score at each time point, two recalls of weekdays and one recall of a weekend day. On the day the 24-h recall is to be completed, an e-mail will be sent to the participant. If the participant fails to complete the R24W, subsequent e-mails will be sent, within 3 weeks (or within the trimester), until three R24W are completed. Detailed reports of energy, macro and micronutrient, are automatically derived from the recall and will also be compiled and analyzed. Furthermore, a new diet quality index reflecting the 2019 Canadian Food Guide might become available to assess diet quality and will be reported if applicable.

Women's urinary dietary exposure biomarker profiles will be analyzed as a secondary assessment of diet quality. A crossover randomized controlled trial published in 2017 demonstrated that urinary metabolic profiling is a precise tool to evaluate dietary intake of the preceding 72 h, that it is sensitive to change, and that it correlates well with the DASH dietary index (61). Participants will collect urine samples on three random days over 1 week at the designated time frame. These spot samples will be pooled after normalizing using refractive index measurement to guide dilution. Around 40 metabolites will be targeted for the quantitative measurement of dietary intake biomarker concentrations. The concentration of dietary intake biomarkers will be measured using Multiple Reaction Monitoring (MRM) methods on a Triple Quadruple LC-MS/MS instrument (47). Each metabolite can be associated with the consumption of a specific food. These foods will then be grouped together into Healthy Eating Index categories to compute a relative dietary quality score (48).

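### The primary mixed model leaves the arms free to differ at time 0, although baseline diet quality is measured before randomisation: a valid analysis, but less efficient than the same data allow

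*Protocol article*

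**What the plan says.** The Primary Outcome Analysis section defines the target: "Our primary endpoint is the difference in the evolution of the HEI score between study groups in time". The mixed linear model for it is described as "integrating the effects of time as a continuous variable, study group, and the interaction between the study group and time". The same section adds a by-visit analysis: "The average HEI score in each group at 2, 4, and 6 months will also be compared using standard mixed-model repeated measures ANOVA". Neither analysis names baseline C-HEI as a covariate or imposes a common baseline mean.

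The Diet Quality section gives the measurement times: "The C-HEI 2007 score will be measured at baseline, 2, 4, and 6 months in preconception". Trial Design and Setting fixes the order of events. Allocation follows once participants have consented, enrolled and "completed baseline assessment, their mobile application profile will be created by the research assistant which will trigger randomization to a treatment group". The randomisation list is blocked but unstratified, so baseline C-HEI is not balanced by design.

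The article does not say outright that the month-0 score is a response in the model. That is inferred from the target being a difference in evolution and from the visit schedule. It is the natural reading, because otherwise the stated model would use no baseline C-HEI at all.

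**The concern.** With time in months from baseline, the coefficient of study group is the difference between the arms at month 0. Randomisation happens after that measurement, so the design already says its expectation is zero. The written model estimates it anyway.

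Two things follow. First, the group-by-time estimate subtracts the observed baseline gap in full, as a change score does, when only a part of that gap carries over to later visits. After a chance imbalance, regression to the mean then appears in the slope contrast. Second, the between-woman information in the post-baseline scores is not used for the treatment contrast.

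At stake is the width of the primary interval and the power of a 68-woman trial whose result is meant to decide whether a larger trial is warranted. The issue is separate from the choice of a linear time trend: all slope figures below assume that the effect really is linear.

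**Working it through.** **Inputs from the article.** Visits at 0, 2, 4 and 6 months; a 10-point difference (10% of a 100-point score); SD 13; alpha 5%, taken as two-sided; 27 women per arm for analysis, 68 recruited (34 per arm).

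**Assumed, because the article does not give it.** Within-woman correlation ρ, with compound symmetry. The effect grows linearly to 10 points at month 6.

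**1. The plan's own figure.** n = 2 × (1.960 + 0.842)² × 13² / 10² = 26.5, so 27 per arm. 54 / 0.8 = 67.5, so 68 in total. Both reproduce.

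**2. Written model (free month-0 difference).** The visit times have mean 3 and sum of squared deviations 9 + 1 + 1 + 9 = 20. The variance of the slope difference is 2σ²(1 − ρ) / (20n). At ρ = 0.5 this is 169 / 540 = 0.313, so the SE is 0.559 per month, or 3.36 points at month 6. Power = Φ(10/3.36 − 1.96) = 84.6%.

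**3. Common month-0 mean.** Fixing the intercept difference at zero multiplies the variance by 1 − r², where r is the correlation of the estimated intercept and slope. For these times, r² = 0.45(1 − ρ) / (0.7 + 0.3ρ). At ρ = 0.5, r² = 0.225/0.85 = 0.265, so the variance falls by 26%. The SE becomes 3.36 × √0.735 = 2.88 and power is 93.5%.

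**4. Range over ρ (outcome SD 13, 27 complete per arm).**

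| ρ | SE written | SE common mean | Power written | Power common mean |
|---|---|---|---|---|
| 0.2 | 4.25 | 3.08 | 65.4% | 90.1% |
| 0.3 | 3.97 | 3.08 | 71.2% | 90.1% |
| 0.4 | 3.68 | 3.01 | 77.6% | 91.3% |
| 0.5 | 3.36 | 2.88 | 84.6% | 93.5% |
| 0.6 | 3.00 | 2.68 | 91.5% | 96.2% |
| 0.7 | 2.60 | 2.40 | 97.0% | 98.6% |
| 0.8 | 2.12 | 2.02 | 99.7% | 99.9% |

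A simulation with 20,000 replicates at ρ = 0.5 gave 84.9% and 93.6% power, and a type I error of 5.0% for both models.

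**5. All 34 per arm complete, ρ = 0.5.** Both SEs shrink by √(27/34), to 2.99 and 2.57. Power is 91.7% and 97.4%, a gain of 5.7 points.

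**6. If 13 is the SD of change.** Its source in Sample Size Calculation is a trial "which demonstrated a 12.5 ± 13.0 points increase in the average HEI score of women with obesity and infertility", which is a change. Then 2σ²(1 − ρ) = 169, and the variance in step 2 is 169/540 whatever ρ is, so the written model has 84.6% power throughout. The common-mean model has 98.4% at ρ = 0.2, 93.5% at 0.5 and 88.0% at 0.8, so the gains are 13.8, 8.9 and 3.4 points. If 13 is both the outcome SD and the change SD, then 13√(2(1 − ρ)) = 13 and ρ = 0.5.

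**7. Effect of a chance imbalance.** One SE of the baseline difference is 13 × √(2/27) = 3.54 points. Given a baseline gap d, the expected later gaps without a treatment effect are ρd. The fitted slope contrast is then −3(1 − ρ)d/20 per month, or −0.9(1 − ρ)d at month 6. With d = 3.54 and ρ = 0.5, this is about −1.6 points.

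**8. One visit compared on its own (t-test, 10 points, 27 per arm, ρ = 0.5).** Unadjusted power is 79%. Adjusting for baseline reduces the SD to 13 × √(1 − 0.25) = 11.3 and power is 89%. At a Bonferroni level of 0.05/3 the figures are 64% and 78%.

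**The case against.** The strongest reply is that nothing here is an error. Time, group and their interaction make a standard longitudinal model, its contrast is unbiased over randomisation, and it keeps its level. It does deal with the baseline gap, by subtracting it. All of that stands. The 1.6-point shift in step 7 is conditional on one observed imbalance and averages to zero over randomisations.

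A reader might infer that the trial is underpowered or that a fixed amount of power, such as 9 points, is lost. The article supports neither. At ρ = 0.5 with 27 complete women per arm, the written model exceeds the planned 80%. It falls below 80% only under added assumptions: ρ of 0.4 or less with 13 as the outcome SD, for instance, or random slopes with an SD of 1 point per month (76% against 86% at ρ = 0.5). Another case is heavy loss. If 15% of 34 per arm have baseline only, 20% reach month 2, 15% reach month 4 and 50% are complete, power at ρ = 0.5 is 75% against 84%. The article states none of these figures. It also plans to use the first pregnancy visit for women who conceive before the 2-month recall, so early conception need not leave baseline only.

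It can also be said that baseline handling belongs in the analysis plan. That has force for the by-visit comparison, where the article is merely silent. It has less force for the primary model, whose fixed terms are listed.

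Finally, a shared baseline mean is justified only if the baseline recalls precede allocation. Each C-HEI score uses three recalls prompted by e-mail, with reminders for up to 3 weeks, and the trial is open label. The article says that baseline assessment is completed first but does not mention the recalls there. This condition needs confirming.

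**Conclusion.** The point holds as an avoidable loss of efficiency, not as an error, a bias or a shortfall against the stated power. The primary model spends information on a month-0 difference that the design makes zero in expectation. Its size cannot be fixed from the article, because the within-woman correlation is not given and the SD of 13 comes from a change. With complete data, compound symmetry and a linear effect, the gain for 27 per arm is about 19 points at ρ = 0.3, 9 at 0.5 and under 2 at 0.7 if 13 is the outcome SD. If 13 is the SD of change, it is about 14 points at ρ = 0.2, falling to 3 at 0.8. Under a linear effect the common-mean model is never less efficient. The conclusion rests on month 0 being a modelled response and on the baseline recalls being finished before allocation. Both are natural readings that the article does not state outright.

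**What to change.** In Primary Outcome Analysis, before data lock:

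- Drop the study-group main effect, so that both arms share one mean C-HEI at time 0. Keep time and group-by-time, and keep the baseline score as an outcome.
- Take the 2-, 4- and 6-month contrasts from a model with the same constraint, or adjust them for baseline C-HEI.
- Confirm that all baseline recalls are completed before allocation. Exclude from the shared-baseline data any recall completed after it.

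The cost is a few lines of analysis wording and a check of recall dates against allocation dates, with no new data, visits or participants. The change should be recorded before results are seen, because a choice of baseline handling made after an imbalance is known would not be credible.

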**For the Preconception Period:**

The primary objective of this trial is to evaluate the impact of the intervention on the diet quality of women measured with the Canadian Healthy Eating Index at 2, 4, and 6 months of follow-up.The secondary objectives of the preconception period are to evaluate the impact of the intervention on:- Urinary metabolomic indicators of women's dietary exposure at 2 months follow-up,- The diet quality of male partners at 2, 4, and 6 months follow-up,- The other lifestyle habits of women and their partners at 3 and 6 months (physical activity, sleep quality, anxious and depressive symptoms, and quality of life),- The anthropometric measures of women and their partners at 3 and 6 months (weight, waist circumference, and body fat percentage), and- The proportion of women and partners with a weight loss of at least 5% body weight at 3 and 6 months.

After completion of the primary outcome assessment, women and their partners who have achieved a pregnancy within 12 months following enrolment will be followed until the end of the pregnancy. Although, there is a potential for unbalanced study groups if the intervention has an impact on fertility, this exploratory follow-up phase will provide preliminary data on the impact of the intervention on lifestyle and clinical outcomes in pregnancy.

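### The supplementary t-tests of mean C-HEI at months 4 and 6 use only women still followed and not yet pregnant; contrasts from a likelihood-based repeated-measures model would use every woman's scores

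*Protocol article*

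**What the plan says.** All references are to the protocol article.

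- **Primary objective** (For the Preconception Period): women's diet quality "measured with the Canadian Healthy Eating Index at 2, 4, and 6 months of follow-up".
- **Primary model** (Primary Outcome Analysis): a "mixed linear model of the HEI score integrating the effects of time as a continuous variable, study group, and the interaction" between group and time. One stated reason is "the different lengths of preconception follow-up that will arise as a result of women becoming pregnant throughout the study"; the other is the variable timing and number of dietary recalls.
- **Supplementary comparison** (same section): "The average HEI score in each group at 2, 4, and 6 months will also be compared using standard mixed-model repeated measures ANOVA", followed by post-hoc Student's t-tests "with Bonferroni correction for multiple comparisons".
- **Early conceptions** (Secondary Outcome Analysis): if a woman conceives before the 2-month recall and/or the 3-month visit, outcomes from her first pregnancy visit complete the preconception analysis. No rule is given for later conceptions.
- **General principle** (Statistical Analysis Plan): results are analysed by intention to treat.

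**The concern.** Two neighbouring sentences do not fit together. The first recognises that conception cuts preconception follow-up short and chooses a model that tolerates this. The second compares visit means with a test that does not.

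A two-sample Student's t-test at month 4 or 6 needs a score at that visit. Women who have conceived by then, and are not covered by the substitution rule, have no preconception score and drop out of the test together with everything they contributed earlier. Those who remain are a subset formed after randomisation. The test also makes no use of baseline C-HEI, which is measured in every woman before randomisation.

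The visit comparisons matter because they are at the time points named in the primary objective. The primary model treats time as continuous and so tests a difference in slope; the visit-by-visit group differences come from this supplementary step. Imprecise or selected month-4 and month-6 differences could disagree with the primary model for reasons unrelated to the intervention.

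**Working it through.** **1. The plan's own figure.** Inputs from Sample Size Calculation: difference 10 points (the stated 10%, read on the 100-point score), SD 13, alpha 5% (taken as two-sided), power 80%, attrition 20%.

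n per group = 2 × (1.960 + 0.842)² × 13² / 10² = 26.5, so 27. Then 27 / 0.80 = 33.75, so 34 per group and 68 in total. Both figures reproduce.

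**2. Women left for the month-6 t-test.** The protocol gives no conception rate, so a range is assumed. With three visit tests (also an assumption), the Bonferroni level is 0.05 / 3 = 0.0167, critical value 2.394. Standard error = 13 × √(2/n); power = Φ(10/SE − critical value).

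| Assumed to conceive by month 6 | n per arm, after 20% attrition | Power at 0.05 | Power at 0.0167 | n per arm, no other dropout | Power at 0.05 | Power at 0.0167 |
|---|---|---|---|---|---|---|
| 0% | 27.0 | 81% | 67% | 34.0 | 89% | 78% |
| 20% | 21.6 | 72% | 55% | 27.2 | 81% | 67% |
| 30% | 18.9 | 66% | 49% | 23.8 | 76% | 60% |
| 40% | 16.2 | 59% | 42% | 20.4 | 69% | 53% |
| 50% | 13.5 | 52% | 35% | 17.0 | 61% | 44% |
| 60% | 10.8 | 43% | 27% | 13.6 | 52% | 35% |

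The exact noncentral t gives values about 1 to 4 points lower (for example 45% and 23% in place of 49% and 27%).

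**3. How much a model would recover.** Assumptions: 27 per arm before conceptions, conception spread evenly over the three intervals and unrelated to C-HEI, equal correlation between visits. The variance of the month-6 contrast comes from the information matrix summed over the follow-up patterns. At correlation 0.5 and level 0.0167:

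| Conceived by month 6 | t-test | Model using earlier follow-up scores | Same model plus baseline |
|---|---|---|---|
| 30% | SE 4.23, 49% | SE 4.09, 52% | SE 3.60, 65% |
| 60% | SE 5.59, 27% | SE 5.15, 33% | SE 4.66, 40% |

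Keeping the earlier follow-up scores alone gains 1 to 12 points over correlations 0.3 to 0.7 and both test levels. Baseline usually adds more.

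**4. When bias appears.** Simulation with 60,000 women per arm, SD 13, correlation 0.5, true differences 3.3, 6.7 and 10 at months 2, 4 and 6. Between 29% and 60% conceive by month 6, with conception depending on the previous score as shown.

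| Conception | t-test, month 6 (true 10) |
|---|---|
| Unrelated to score or arm | 10.0 to 10.1 |
| Related to score, equally in both arms | 10.0 |
| Related to score, plus an arm effect | 9.2 to 9.5 |
| Related to score in the intervention arm only | 8.3 to 8.9 |
| Strongly related in the intervention arm only, plus an arm effect | 5.8 to 7.1 |

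A likelihood fit with visit as a category returned 9.9 to 10.2 in every row. That is expected: conception was made to depend on observed scores, which is the missing-at-random condition such a fit needs.

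**The case against.** **The ANOVA may already be likelihood-based.** This stands. A reader might infer that the ANOVA drops every woman with a missing visit. The classical version would, but the protocol says mixed-model, and a likelihood fit keeps partial records. Loss of women is established only for the t-tests. The article may even be using that term for model contrasts; if so, the fix is a change of wording.

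**The primary analysis is already protected.** This also stands. The visit means are compared in addition, and nothing here weakens the primary mixed model.

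**The size is not known.** A reader might infer that the trial expects many women to conceive before month 6. The protocol says only that conceptions will occur throughout the study, and requires an intention to conceive within 12 months. The rates above are assumptions.

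**Bias is not shown.** A reader might cite the admission that "there is a potential for unbalanced study groups if the intervention has an impact on fertility". That sentence concerns the exploratory pregnancy follow-up, not the month-4 and month-6 contrasts. The same mechanism could reach those visits, but the protocol does not say so, and the simulation shows no bias when the dependence is absent or equal in both arms.

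**The low power is mostly not due to the t-tests.** Largely right. With no conceptions, power at 0.0167 is already 67% from 27 per arm. The fix keeps the correction and cannot create scores for women who conceived.

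**The remedy has its own assumption.** True, and it should be stated. It does not favour the t-test, which needs the stronger condition that the women remaining at each visit give a fair comparison of the arms.

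**Conclusion.** The point holds in limited form. The Student's t-tests at months 4 and 6 are a weaker method than the one the same section justifies a sentence earlier. They rest on a post-randomisation subset, leave baseline unused and discard the earlier scores of women who conceived, and there is no rule for conceptions after the window covered by the substitution.

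The certain cost is precision. Under the assumptions in step 3, the month-6 standard error is 4.23 against 3.60 with 30% conceiving, and 5.59 against 4.66 with 60%. Most of that gain comes from baseline adjustment, the smaller part from keeping earlier scores. Bias is possible but conditional: none when conception is unrelated to diet quality or equally related in both arms, and up to about 4 of 10 points in the most extreme simulated case (5.8 against 10). The real size cannot be fixed without a conception rate. The primary conclusion of the trial does not depend on this. It is worth changing because the better method is free.

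**What to change.** Replace the ANOVA and t-tests with group differences at 2, 4 and 6 months taken as contrasts from one likelihood-based repeated-measures model: visit as a category, group, group by visit, baseline C-HEI as covariate, and all available scores from all randomised women. Apply the Bonferroni correction to those three contrasts.

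Add a sentence on how conception before months 4 and 6 is handled, and say which visits the existing first-pregnancy-visit substitution fills. State that the contrasts assume missingness at random and refer to the score expected had preconception follow-up continued.

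The cost is two or three sentences in the analysis plan, with no new data, no more participants and no change to the primary model.

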**For Pregnancy:**

The main secondary objective of this phase is to explore the impact of the intervention on the proportion of women whose gestational weight gain conforms to the guidelines of the *National Academy of Medicine* recommendations (46).The other secondary objectives of the pregnancy period are to explore the impact of the intervention on:- The trajectory of dietary and lifestyle habits of women and their partners in the first, second, and third trimesters,- Women's urinary dietary exposure metabolomic profile at 24–26 weeks of pregnancy,- The change in the anthropometric measures (weight, body fat percentage, and waist circumference) of partners between the first and third trimesters,- The proportion of partners with overweight or obesity at study enrolment who have a weight loss of at least 5% body weight in the first, second, and third trimesters,- Perinatal morbidity indicators (gestational diabetes, hypertensive disorders of pregnancy, gestational age at delivery, delivery mode, birthweight, and neonatal hypoglycemia),- Fertility outcomes (viable pregnancy rate, spontaneous abortion rate, and live birth rate).

Women's diet quality will also be assessed based on metabolomic analysis of urinary samples. We will establish a profile of dietary exposure biomarkers, which will be used to compile a metabolite derived diet quality score (47, 48). This exploratory analysis will provide important data to support its use in a future larger multicenter trial.

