#### Secondary Outcome Analysis

For the main secondary outcome for the pregnancy phase of the trial, we will use a Chi-squared test to compare the proportion of women who have an adequate gestational weight gain in each group.

For the targeted analysis of urine biomarkers, the concentration of around 40 metabolites will be compared between baseline, 2 months in preconception and 24–26 weeks of pregnancy using repeated measures ANOVA or Friedman test with a Bonferroni adjustment for multiple comparisons. The correlation between the metabolite derived diet quality score and the C-HEI score will be evaluated using Pearson's correlation.

Although our sample size is fairly small, an exploratory multivariate analysis of non-targeted metabolome profiles will be realized using both unsupervised ‘natural clustering’ analysis and Supervised Random Forest classification.

For the other secondary outcomes, continuous variables will be assessed using Student's *t*-tests or Mann-Whitney tests as appropriate. Dichotomic variables will be analyzed using Chi-squared tests or Fisher's exact test as appropriate.

For participants who achieve a pregnancy prior to the 2-month food recall and/or 3-month preconception visit, lifestyle and anthropometric outcomes at the first pregnancy visit will be used to complete the preconception analysis. Women will be able to signal the occurrence of a pregnancy through the mobile application as soon as a period is missed. The application software will immediately notify the research team which will allow completion of data collection prior to the occurrence of significant pregnancy symptoms such as hyperemesis.

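### The supportive 2-, 4- and 6-month comparisons of the diet score use single-step Bonferroni where Holm gives the same error control and is never less powerful

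*Protocol article*

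**What the plan says.** The Primary Outcome Analysis section makes the primary test a single one: the group-by-time interaction in a linear mixed model with time as a continuous variable. It then adds a comparison of the group means at 2, 4 and 6 months, by repeated-measures ANOVA followed by post-hoc t-tests "with Bonferroni correction for multiple comparisons". The primary objective for the preconception period names the same three time points.

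The Sample Size Calculation section is built on one unadjusted comparison: "To detect a 10% difference in the average HEI score between groups", "with a 13-point standard deviation", "an alpha value of 5% and 80% power", giving the statement "we will need to recruit 27 women per group".

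The Secondary Outcome Analysis section compares around 40 urinary metabolites across baseline, 2 months and 24–26 weeks of pregnancy, again "with a Bonferroni adjustment for multiple comparisons". No step-down method is mentioned in either place.

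**The concern.** Single-step Bonferroni holds each of the three visit comparisons to 0.05/3 = 0.0167, however strong the evidence at the other visits. Holm starts at the same threshold for the smallest p-value, then relaxes to 0.05/2 and 0.05 for the next two as long as each step rejects. Its family-wise error guarantee is the same and also needs no assumption about correlation between visits. Any power lost by choosing Bonferroni therefore buys nothing in error control.

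At stake is how well the trial can say at which of the named time points the groups differ. The trial is small, and follow-up shortens as women conceive. The interaction test shows whether the trajectories diverge; the visit contrasts are what locate the difference.

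**Working it through.** **Inputs from the protocol article.** Difference 10 points: the stated 10% is read as 10 points because the C-HEI is described as one "which is a 100-point score adapted from the American HEI-2005". SD 13, alpha 5%, power 80%, 27 per group, 20% attrition, 68 in total, three visits.

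**Assumptions not in the document.** Two-sided tests; the Bonferroni family is the three between-group visit contrasts; correlation between the visit test statistics of 0.3 to 0.7; 27 evaluable women per group at every visit.

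**1. The plan's figure.** n per group = 2 × 13² × (1.960 + 0.842)² / 10² = 26.5, so 27. Then 54 / (1 − 0.20) = 67.5, so 68. Both stated figures reproduce.

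**2. Power of one visit comparison.** Standard error = 13 × √(2/27) = 3.54; 10 / 3.54 = 2.826.
- At 0.05: Φ(2.826 − 1.960) = 80.7% (79.2% by noncentral t).
- At 0.0167: Φ(2.826 − 2.394) = 66.7% (63.8% by noncentral t).
- For 80% power at 0.0167: 2 × 13² × (2.394 + 0.842)² / 10² = 35.4, so 36 per group.

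**3. Bonferroni against Holm across the three visits** (simulated normal test statistics; correlation 0.5 except where noted).

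| True difference at 2, 4, 6 months | Bonferroni, power per visit | Holm, power per visit | At least one visit significant |
|---|---|---|---|
| 10, 10, 10 | 67% each | 74–75% each (correlation 0.3 to 0.7) | 87.9% with both |
| 3.3, 6.7, 10 | 7%, 31%, 67% | 13%, 36%, 68% | 71.1% with both |
| 0, 0, 10 | 67% at 6 months | 67% at 6 months | 68.1% with both |

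A separate simulation using t-tests (correlation 0.4 to 0.6) gave 64% against 73% per visit in the first scenario. With no true effect, family-wise error is below 5% for both methods (4.0–4.8% for correlations 0.7 to 0.3).

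The last column is equal by construction: Holm's first step is the Bonferroni threshold, so it can add rejections only after Bonferroni has made at least one.

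**4. Metabolites.** If the family is the 40 metabolites, the threshold is 0.05/40 = 0.00125. With 5, 10 or 20 true effects and assumed noncentrality of 2.8 or 3.5, average power under Bonferroni is about 33–34% or 61%. Holm adds about 0.3 to 4 points. The gain is small because, with 40 tests, the step-down threshold relaxes slowly.

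**The case against.** The strongest reply is that nothing here is wrong. Bonferroni is valid, the visit t-tests are post hoc and supportive, and the interaction test and the sample size are unaffected. All of that stands, and it is why the point concerns efficiency only.

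The larger gain is also a favourable case. It needs the full 10 points already at 2 months and 27 evaluable women per arm at each visit. The two results behind the planning effect are changes after 6-month interventions, so a growing effect is at least as plausible; the gain at 6 months is then about 1 point. This too stands. It limits the size of the benefit, but it does not give a reason to prefer Bonferroni.

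Two stronger readings are tempting and the document does not support them:

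- **That Bonferroni weakens the primary result.** A reader might infer this because the primary objective names 2, 4 and 6 months. The primary test is the single interaction, which carries no adjustment.
- **That the metabolite analysis is far too strict and should move to false discovery rate control.** The text does not say whether the adjustment spans the 40 metabolites, the pairs of time points or both, so 0.00125 is only one reading. It describes a comparison over time with no group factor stated, so a two-arm power figure based on the diet-score effect does not represent it. The urinary indicators are listed as a secondary objective. The sentence "This exploratory analysis will provide important data to support its use in a future larger multicenter trial" concerns the biomarker profile used to build a diet score. Benjamini-Hochberg at 5% would add about 12–33 points of average power in the simulations above, but with family-wise error of about 11–38%. That is a trade-off for the sponsor to weigh, whereas Holm gives up no error control.

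**Conclusion.** The point holds as an optional improvement. For the three visit contrasts, Holm is at least as powerful as Bonferroni in every scenario, at the same family-wise error. The gain is about 7–9 points per visit if the 10-point difference is present throughout, about 1–6 points per visit if the effect grows linearly to 10 points, and essentially nil if only one visit carries an effect. The chance of at least one significant visit, the primary test and the sample size do not change.

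The direction of the result needs no assumption. Its size depends on the assumed correlation, the shape of the effect over time and 27 evaluable women per arm at each visit; pregnancies will reduce that number at later visits.

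**What to change.** In Primary Outcome Analysis, replace Bonferroni by Holm and state that the family is the three between-group contrasts at 2, 4 and 6 months. This is a one-word change plus a clause, to be made before the data are analysed. It costs nothing in error rate or power; simultaneous confidence intervals matching Holm are less simple than Bonferroni intervals.

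In Secondary Outcome Analysis, Holm may likewise replace Bonferroni for the metabolites, with a statement of which tests form the family; the expected gain is small. Benjamini-Hochberg is an option only if the sponsor decides, and says, that this set is an exploratory screen. It is not part of the fix.
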